#### Course of the study

All LT patients who meet our inclusion/exclusion criteria will be informed about the study procedures and their potential benefits. Possible side effects will be clearly declared. Then the patients will be asked to give written consent to participate in the trial via a trial investigator. Baseline clinical and demographic data of the eligible patients will be recorded. Laboratory data will be recorded using routine laboratory tests, which will be performed over the course of the perioperative clinical routine. The patient will be randomized to one of the study arms according to the randomization protocol, and the surgical team will be informed at the time of operation. Figure 1 shows the trial flow diagram.

**Fig. 1 Fig1:**
[figure not shown]
Flowchart of the SEALIVE trial according to Consolidated Standards of Reporting Trials (CONSORT) guidelines

The entire BL from skin incision to skin closure is defined as “intraoperative BL.” To assess the exact amount of hemorrhage, the volume of fluid in the suction container(s) that are used during the procedure will be recorded in a case report form (CRF) at the end of skin closure procedures. All ascites will be evacuated after opening the abdomen, and the respective amount in milliliters will be documented. Furthermore, the numbers of all small and big surgical swabs will be recorded. All swabs together will be weighed by the end of skin closure procedures along with the drip-catching container in which they are collected. The exact weight in grams will be recorded in the CRF. The exact amount of rinse fluid in milliliters that is used during the procedure will also be recorded in the CRF.

The calculation of total BL will be as follows. The suction container fluid volume (in milliliters) will be added to the weight (in grams) of all surgical swabs at the end of skin closure procedures (A). The difference of the density of the rinse solution (isotonic sodium chloride solution) and blood is approximately 0.055 g/cm^3^. Regarding the accuracy of these measurements, this difference is clinically irrelevant.

The volume of the entire rinse fluid (in milliliters) that is used during the procedure and the amount of ascites (in milliliters) will be added to the known dry weight (in grams) of the respective number of surgical swabs that are used during the procedure and the known dry weight of the drip-catching swab container (B). The total BL is defined as “A” minus “B” in milliliters. Protocol deviations will be recorded.

After the transplant, the routine care protocols (the same as other LT patients) will be performed, and at each visit, the patient will be assessed for BL, transfusion, and postoperative complications. The laboratory tests, including PTT and INR, will be performed in the clinical routine prior to operation as well as 1, 3, 7, and 10 days after operation and at discharge. During the study period, all postoperative surgical complications will be recorded. All study-related data will be handled and stored by the KSC data center. The enrollment period is estimated to be 36 months, with the last patient being enrolled at 39 months.

### Monitoring

Surgical monitoring will be done by intraoperative photographs (to be taken by a member of the KSC) of the procedure being performed according to the randomization result. This will include the situs after opening the abdominal wall, the use of the instrument in the experimental arms, and the ventral surface of the caval vein after removal of the recipient’s liver.

#### Patient time schedule and documentation

##### Visit day − 1

After the inclusion and exclusion criteria are evaluated, if patients are eligible for participation in the study, the following baseline data will be documented:

Demographic characteristics:Gender (female/male)Age (years)Height (cm)Weight (kg)

Baseline clinical data:Reason for transplantModel for End-Stage Liver Disease scoreBaseline laboratory valuesAmerican Society of Anesthesiologists score (according to the anesthesiologist’s protocol)Comorbidities (cardiac, pulmonary, renal, autoimmune, hematologic, and infectious; previous abdominal surgery)Medication

##### Visit day of surgery

The following data will be recorded intraoperatively according to the study endpoints:Duration of hepatectomyDuration of whole procedureBL during the hepatectomyBL during whole procedureTransfusion requirements of PRBC and FFPHemodynamic status during hepatectomy and whole procedure (including CVP)Presence of portal venous cavernous transformation and/or umbilical varicesFeasibility of trial methods (rate of conversion to alternative methods during recipient hepatectomy in the LS, USD, and control groups, as well as protocol violations)Documentation of the surgeon’s experience in LT (number of cases) and the user’s experience with the applied method (frequent/rare)

##### Visit PODs 1, 3, 5, 7, and 10 and day of discharge

The following data will be recorded postoperatively or taken during the patient’s hospital stay:Transfusion requirementsHb and platelet count, coagulation parametersSurgical complications (i.e., bleeding at site of LS and USD use)Serious adverse events (SAE)/treatment-emergent adverse events (TEAE)

##### Visit PODs 30 and 90

SAE/TEAE, complications, and mortality will be recorded until POD 90. Figure 2 gives an overview of study visits and documentation of data for each patient.

**Fig. 2 Fig2:**
[figure not shown]
Visit schedule and documentation according to the Standard Protocol Items: Recommendations for Interventional Trials (SPIRIT) guidelines

##### Accompanying therapy

The participant will receive routine care and treatment according to the University Hospital Heidelberg’s manual for LT [27].

##### Safety laboratory

Not applicable.

##### Safety objectives and assessment of safety

To assess the safety of the surgical procedures under investigation, all incidences of TEAEs and SAEs will be documented and evaluated. We will collect only intervention-related events that occur during surgery and follow-up. All TEAEs/SAEs and intervention-related adverse effects will be documented on separate forms and analyzed as part of the safety analysis.

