**Methods/design:**

In a single-center, prospective, randomized, controlled, parallel, three-armed, confirmatory, open trial, LigaSure™ and HARMONIC ACE®+7 will be compared with standard surgical techniques that use titanium clips and conventional knot-tying ligations during recipient hepatectomy in liver transplantation. Intraoperative total blood loss is the primary endpoint of the trial. Secondary endpoints include blood loss during hepatectomy, the duration of both the hepatectomy and the entire surgical procedure, and blood transfusion requirements of the procedure. To generate reliable data, intraoperative blood loss will be recorded with respect to all rinse fluids during surgery, ascites, and by weighing used swabs. At 80% power and an alpha of 0.025 for both of the experimental groups, 23 subjects will be analyzed per protocol in each study arm in order to detect clinically relevant reduction of intraoperative blood loss. The intention-to-treat analysis will include 69 patients. The follow-up period for each patient will be 90 days for safety reasons, whereas all clinical outcomes will be measured within the first 10 postoperative days.

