##### SAEs

SAEs are defined as any untoward medical occurrence that meets one or more of the following criteria:Results in deathIs life-threateningRequires inpatient hospitalization or prolongation of existing hospitalizationResults in persistent or significant disability/incapacityRequires other intervention(s) to prevent persistent impairment or damage

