##### Documentation of SAEs

From the time that the patient approves and signs the informed consent to either the study’s end or the patient’s withdrawal, SAEs must be documented on an SAE form available in the investigator study file. All SAEs that occur from the time between the day of inclusion and discharge must be documented on an SAE form in the CRF. The SAE form will contain the following information: the name of attending physician, a detailed description of the SAE (including event, beginning and duration, severity, outcome, causality to trial intervention, therapy/interventions taken), the consequence for the trial, and a dated signature of the attending physician.

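### The safety section requires all adverse events and then only intervention-related ones; following the narrow sentence would lose events and could bias the arm comparison

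*Protocol article*

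**What the plan says.** **Which events.** Three consecutive sentences under Safety objectives and assessment of safety set the scope:

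- first, "all incidences of TEAEs and SAEs will be documented and evaluated";
- second, "We will collect only intervention-related events that occur during surgery and follow-up";
- third, "All TEAEs/SAEs and intervention-related adverse effects will be documented on separate forms and analyzed as part of the safety analysis".

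The next section, SAEs, gives the definition: "SAEs are defined as any untoward medical occurrence that meets one or more of the following criteria". Relatedness is not among the criteria. Documentation of SAEs makes causality one of the items on the SAE form, and Classification of SAEs gives it four classes: unrelated, possibly related, definitely related and not assessable.

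**For how long.** Documentation of SAEs first runs from consent "to either the study’s end or the patient’s withdrawal", on a form kept in the investigator study file. Its next sentence reads "All SAEs that occur from the time between the day of inclusion and discharge must be documented", on an SAE form in the CRF. The text for the POD 30 and 90 visits says "SAE/TEAE, complications, and mortality will be recorded until POD 90". Methods of data collection runs to the end of each patient's follow-up, which the abstract puts at 90 days.

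**The concern.** The second sentence on scope restricts collection to events with a particular cause, while the sentences on either side of it do not. Staff cannot follow both rules. Someone who follows the narrow one must decide whether an event is related before deciding whether to record it.

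The setting makes this more than a matter of wording. The Blinding section says that the surgical staff cannot be blinded. Under Reporting of SAEs the attending physician reports the event together with a causality assessment. Study termination says that no data monitoring committee is needed. Under the narrow rule, a judgement made with knowledge of the arm would determine whether an event exists in the data at all. It may then be impossible to recover an unrecorded event or to reassess its cause. If relatedness is judged differently for a new device than for clips and ligatures, the recorded counts would differ between arms even where the true rates are equal.

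On timing, if the CRF holds SAEs only up to discharge, the period covered by the CRF data depends on length of stay, which can differ between patients and between arms.

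**Working it through.** The protocol gives no safety figure to reproduce, so the check is mainly a comparison of passages.

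**Scope**

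| Place in the protocol | Rule | Limited to related events? |
|---|---|---|
| Safety objectives, 1st sentence | all TEAEs and SAEs | no |
| Safety objectives, 2nd sentence | only intervention-related events | **yes** |
| Safety objectives, 3rd sentence | all TEAEs/SAEs, with intervention-related effects as a further item | no |
| SAEs | any untoward occurrence meeting a seriousness criterion | no |
| Documentation of SAEs | causality is a field on the form | no |
| Classification of SAEs | includes a class for unrelated SAEs | no |
| Methods of data collection | every SAE goes on the form | no |
| Reporting of SAEs | causality is assessed within the report | no |

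One sentence is out of line with the rest. Under it the unrelated class could never be used. It also leaves open whether possibly related and not assessable events count as intervention-related.

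**Window**

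| Place in the protocol | End of SAE recording |
|---|---|
| Documentation of SAEs, 1st sentence (investigator study file) | study end or withdrawal |
| Documentation of SAEs, 2nd sentence (CRF) | **discharge** |
| Visit PODs 30 and 90 | POD 90 |
| Methods of data collection | end of follow-up |

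Three of the four agree on the long window. No sentence places SAEs after discharge in the CRF.

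**Illustration of size.** The protocol gives neither an SAE rate nor a share judged related, so both are assumptions here. Only the 23 patients per arm comes from the protocol (Sample size estimation).

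- Expected recorded = 23 × true SAE rate × share judged related.
- Spurious difference = true SAE rate × (share in arm 1 − share in arm 2), with the true rate equal in both arms.

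| True SAE rate, both arms | All SAEs recorded, per arm | Recorded at shares 30% and 10% | Spurious difference |
|---|---|---|---|
| 30% | 23 × 0.30 = 6.9 | 6.9 × 0.3 = 2.1; 6.9 × 0.1 = 0.7 | 0.30 × 0.20 = 6 points |
| 50% | 23 × 0.50 = 11.5 | 11.5 × 0.3 = 3.4; 11.5 × 0.1 = 1.2 | 0.50 × 0.20 = 10 points |
| 70% | 23 × 0.70 = 16.1 | 16.1 × 0.3 = 4.8; 16.1 × 0.1 = 1.6 | 0.70 × 0.20 = 14 points |

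With shares of 40% and 10% the differences are 9, 15 and 21 points. With 30% in both arms the difference is 0, but 70% of events go unrecorded. The sign reverses if the device is excused rather than blamed. The calculation treats each patient as having one event; a patient with several SAEs drops out only if all of them are filtered.

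**The case against.** The strongest reply is that the protocol as a whole operates the broad rule. No passage describes a screening step before recording. Causality is filled in on the form, after the event has been captured, and the sections on definition, documentation, classification and reporting all fit that. On this view the narrow sentence is a slip that staff may never act on. This stands as far as it goes: the filtering is what would follow from obeying the sentence, not a procedure that the protocol sets out. The sentence is still explicit, says only, and is not limited to non-serious events, so it cannot be read away.

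Four stronger readings are tempting, and the document does not support them.

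- *SAE recording stops at discharge, so late events and deaths are lost.* The discharge sentence concerns the CRF form and may be only a filing rule. The sentence before it, the POD 90 visit text and Methods of data collection all run longer.
- *The abstract's statement that "all clinical outcomes will be measured within the first 10 postoperative days" contradicts the 90 days.* The same sentence sets 90 days of follow-up for safety and contrasts it with the clinical outcomes. It separates the two.
- *The SAE counts are the only basis for stopping the trial.* Study termination also names mortality and external evidence, and mortality is recorded to POD 90.
- *All comparison of surgical harm depends on the SAE filter.* Course of the study has every postoperative surgical complication recorded, and the secondary endpoints include graded bleeding and morbidity, with no relatedness condition.

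**Conclusion.** The scope contradiction is established by the text. If the narrow sentence were followed, any event judged unrelated would be lost, and the comparison of SAEs between arms could be biased. Bias is possible, not certain: it needs relatedness to be judged differently by arm. Its size and direction are unknown, and it is zero if the arms are judged alike. The 6 to 14 points (up to 21 with the wider shares) show only what assumed rates would produce.

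The window point is real but lesser. The long window is clearly intended; what is unclear is whether SAEs after discharge reach the CRF.

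Neither point touches the primary endpoint, intraoperative blood loss. Both concern the safety analysis.

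**What to change.** 1. Delete the sentence under Safety objectives and assessment of safety that restricts collection to intervention-related events.
2. State one rule: all SAEs are recorded in all three arms regardless of causality, with causality kept as a recorded attribute using the four existing classes. Related events can then be analysed as a subset.
3. In Documentation of SAEs, replace discharge as the end of CRF recording with POD 90, the limit already stated for the POD 30 and 90 visits.

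The cost is protocol and CRF wording plus some additional SAE forms. The POD 30 and POD 90 visits are already planned, so no new visit is needed.

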##### SAEs

SAEs are defined as any untoward medical occurrence that meets one or more of the following criteria:Results in deathIs life-threateningRequires inpatient hospitalization or prolongation of existing hospitalizationResults in persistent or significant disability/incapacityRequires other intervention(s) to prevent persistent impairment or damage

##### Documentation of SAEs

From the time that the patient approves and signs the informed consent to either the study’s end or the patient’s withdrawal, SAEs must be documented on an SAE form available in the investigator study file. All SAEs that occur from the time between the day of inclusion and discharge must be documented on an SAE form in the CRF. The SAE form will contain the following information: the name of attending physician, a detailed description of the SAE (including event, beginning and duration, severity, outcome, causality to trial intervention, therapy/interventions taken), the consequence for the trial, and a dated signature of the attending physician.

##### Classification of SAEs

Classification of outcome: The outcome of an SAE at the time of last contact with the patient is classified as follows:Ongoing: Signs and symptoms of the SAE continue.Recovered completely: All signs and symptoms of the SAE have disappeared.Recovered with sequelae: Acute signs and symptoms of the SAE have disappeared, but the sequelae caused by the SAE still exist.Death: The SAE has caused the patient’s death. If a subject has experienced more than one SAE, only the outcome for the SAE directly responsible for death is classified as “death,” whereas the other SAEs are classified according to their specific outcome.Unknown: The outcome is unknown or is implausible, and there is no possibility to complete or verify the information.Classification of intensityMild: a temporary event that is well tolerated by the subjectModerate: an event that results in discomfort for the subject and impairs his/her normal activitySevere: an event that results in substantial impairment of normal activities of subjectClassification of causalityUnrelated: an SAE that does not follow a reasonable temporal sequence from trial treatment and that is likely to have been produced by the subject’s clinical state, other modes of therapy, or other known etiologyPossibly related: An SAE that has a reasonable possibility of having been caused by trial treatment. The SAE has a timely relationship to trial treatment(s); however, the event follows no known pattern of response, and an alternative cause seems more likely or there is significant uncertainty about the cause of the event.Definitely related: There is a reasonable possibility that the event may have been caused by trial treatment. A certain event has a strong temporal relationship, and an alternative cause is unlikely.Not assessable: There is insufficient or incomplete evidence to make a clinical judgment regarding the causal relationship to trial treatment.Classification of countermeasures: The countermeasures will be documented according to the following rules:None: no action takenDrug treatment: newly prescribed medication or change in dose of a medicationOthers: other countermeasures (e.g., an operative procedure)

#### Methods of data collection

SAEs will be documented until the end of follow-up of each patient. The results will be evaluated in the clinical results report. Each patient will be asked to report the occurrence of any event to the investigator. At each visit, the investigator will ask the patient if he or she has experienced any of the SAEs noted since the last visit. Each SAE must be reported in the SAE form available in the investigator study file.

#### Reporting of SAEs

SAEs must be reported by the attending physician to the principal investigator within 24 hours after the SAE becomes known. The initial report must be as complete as possible, including details of the current illness, the SAE, and an assessment of the causal relationship between the event and trial treatment.

#### Emergency treatment

During and following the subject’s participation in the trial, the investigator must ensure that adequate medical care is provided. The subject must receive adequate treatment in any clinical situation, including any emergencies and outcomes of the patient that must be checked.

#### Termination criteria

##### Study termination

To assess the trial’s safety, deaths and SAEs will be documented on separate forms and analyzed within the safety analysis. The principal investigator, in consultation with key research associates and the biostatistician, may terminate the trial at any time. Reasons for termination may include high mortality rate as well as incidence or severity of SAEs that indicate a potential health hazard caused by either the study treatment or external evidence which requires premature termination of the trial. Due to the open nature of the trial and the use of fully approved techniques, a data monitoring committee is not necessary in this single-center trial.

#### Patients’ withdrawal

A patient is taken out of the study if he/she withdraws his/her consent to participate at any time without the need to state the reason and without disadvantages for further medical care. The withdrawal of a patient will be documented in the CRF.

#### Statistical design

Dichotomous data and counts will be presented as frequencies. Continuous data will be presented as mean with SD or as median value with a range. Statistical interpretation of the data includes multiple *t* tests with Bonferroni correction for parametric data (including BL) and the Kruskal-Wallis test for nonparametric data. The chi-square test will be used for categorical data. The significance level will be set at alpha ≤ 0.05 (after a Bonferroni adjustment when applicable) representing 95% confidence.

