#### Secondary endpoints

BL during recipient hepatectomyTime from skin incision to end of hemostasis after hepatectomyTime from skin incision to end of skin closureHemodynamic status during surgery: Data on the mean arterial pressure and central venous pressure (CVP) will be obtained at the beginning of hepatectomy after incision and adhesiolysis.Coagulation state: International normalized ratio (INR), partial thromboplastin time (PTT), and platelet counts of patients will be recorded pre- and postoperatively until postoperative day (POD) 10.Hemoglobin (Hb) level: Hb levels of patients will be recorded pre- and postoperatively until POD 10.The number of units of packed red blood cells (PRBC) transfused during surgeryThe number of fresh frozen plasma (FFP) units transfused during surgeryThe number of platelet units transfused during surgeryPostoperative PRBC and FFP transfusion until POD 10Postoperative bleeding: Postoperative hemorrhaging until POD 10 will be recorded and classified as defined by Dindo et al. [21].Postoperative morbidity: Postoperative morbidity will be recorded and classified as defined by Dindo et al. [21].Retransplant rateConversion rate to alternative methods during recipient hepatectomy in LS and USD groups

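### Secondary laboratory endpoints (Hb, INR, PTT, platelets): the tests named have no covariate or repeated-measures term, and no time point or summary is named, so precision may be lost

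*Protocol article*

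**What the plan says.** Secondary endpoints in the Protocol article defines coagulation state through three variables: "International normalized ratio (INR), partial thromboplastin time (PTT), and platelet counts of patients will be recorded pre- and postoperatively until postoperative day (POD) 10". It defines the Hb endpoint in the same way: "Hb levels of patients will be recorded pre- and postoperatively until POD 10". Baseline laboratory values are also collected at the visit on the day before surgery.

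The postoperative time points appear in two places. Course of the study puts the laboratory tests "prior to operation as well as 1, 3, 7, and 10 days after operation and at discharge". The visit schedule, under "Visit PODs 1, 3, 5, 7, and 10 and day of discharge", lists Hb, platelets and coagulation parameters and so includes POD 5.

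Statistical design assigns tests by type of data. It opens with "Statistical interpretation of the data includes multiple" t tests, to be used with "Bonferroni correction for parametric data (including BL) and the Kruskal-Wallis test for nonparametric data", and closes the list with "The chi-square test will be used for categorical data". It names no analysis of covariance, mixed model or other repeated-measures method. It also does not say which number per patient (a single visit, a change from the preoperative value, or an average over visits) enters the laboratory comparisons.

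**The concern.** These four variables are defined as series with a preoperative value, but the tests named for continuous data compare independent groups on one number per patient. Applied to the raw value at a visit, they use neither the preoperative measurement nor the other visits.

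What is at stake is precision and a single defined answer per variable. Arms of 23 are small, Randomization protocol describes blocks but no stratification, and the article's Discussion describes recipients with coagulopathy and thrombocytopenia. To the extent that preoperative values predict postoperative ones, chance differences between arms add noise to the comparison, and data already collected could remove it.

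**Working it through.** **Inputs.** n = 23 per arm (Sample size estimation; Randomization protocol). There are two device-versus-control comparisons (Hypotheses). Two-sided alpha of 0.025 per comparison and 80% power come from Sample size estimation; they are set there for blood loss and borrowed here only for illustration. The article states no effect size, SD or correlation for any laboratory variable, so there is no figure of its own to reproduce. All correlations below are assumptions. Differences are in units of the SD at one visit.

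**1. t test at one visit.** SE of a difference between two arms = √(2/23) = 0.295 SD. Detectable difference = (2.241 + 0.842) × 0.295 = 0.91 SD (normal approximation).

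**2. One visit, preoperative value as covariate.** The variance left is 1 − r², where r is the correlation between the preoperative value and the value at that visit. The detectable difference is 0.91 × √(1 − r²). The arm size that would give the same precision without adjustment is 23/(1 − r²). The last column gives a t test on change from the preoperative value, with variance 2(1 − r) if the SD is the same before and after surgery.

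| Assumed r | Variance left, ANCOVA | Detectable difference | Equivalent n per arm | Variance, change score |
|---|---|---|---|---|
| 0.2 | 0.96 | 0.89 SD | 24 | 1.60 |
| 0.3 | 0.91 | 0.87 SD | 25 | 1.40 |
| 0.5 | 0.75 | 0.79 SD | 31 | 1.00 |
| 0.7 | 0.51 | 0.65 SD | 45 | 0.60 |

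A change score does use the preoperative value, but it is less precise than the raw postoperative value when r is below 0.5, and less precise than ANCOVA at every r in the table.

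**3. Average of m postoperative visits, preoperative value as covariate.** With correlation v between postoperative visits and b between the preoperative value and each visit, the variance left is (1 + (m − 1)v)/m − b². For m = 4 (POD 1, 3, 7, 10):
- v = b = 0.5: (1 + 1.5)/4 − 0.25 = 0.375.
- v = 0.7, b = 0.2: (1 + 2.1)/4 − 0.04 = 0.735.

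The gain therefore depends strongly on assumptions that the article cannot settle.

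**4. Chance imbalance before surgery.** P(difference of at least 0.5 SD in either direction) = P(|Z| ≥ 0.5/0.295) = about 9% per contrast. The expected carry-over into the postoperative difference is r × 0.5 SD: 0.10 SD at r = 0.2 and 0.35 SD at r = 0.7. The unadjusted SE already allows for this. It is noise, not bias.

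**5. The two visit lists.** Course of the study gives POD 1, 3, 7, 10 and discharge. The visit schedule gives POD 1, 3, 5, 7, 10 and discharge. They differ on POD 5, so the set of visits for any repeated-measures analysis is not fixed.

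**The case against.** The strongest objection is that this is detail an article may leave to a fuller document. The list of tests is introduced as what the analysis includes, not as everything it contains. Blood loss is the only variable tied by name to a test, and the hypotheses concern blood loss alone. The named tests can also be run on a change score or a mean over visits, which would use the preoperative value or the repeated measurements. Preoperative values may predict postoperative ones poorly, because the diseased liver is replaced in between and blood products may be given. At r = 0.2 the adjustment saves only 4% of the variance.

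Most of this stands, and it limits the point. Three stronger readings should not be drawn from the text:
- A reader might infer that every visit will be tested separately: 4 variables × 5 visits × 2 contrasts = 40 t tests (32 with four visits). The article does not say so. Kruskal-Wallis would be one three-group test per visit (4 × 5 = 20), and the t tests carry a Bonferroni correction.
- A reader might infer that the plan intends to disregard the preoperative data. It leaves the summary open, which is different.
- A reader might infer that the comparisons would be biased or invalid. They would not be: two-sample and rank tests are valid under randomisation.

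What remains is that Statistical design is not silent on continuous outcomes. It names specific tests, none with a covariate or repeated-measures term, and pairs them with no summary that would make up for this.

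**Conclusion.** The point holds as a minor improvement in efficiency and definition. For Hb, INR, PTT and platelets, the named tests give up precision unless they are applied to a summary that the text does not name. At a single visit, adjustment for the preoperative value leaves about 96%, 75% or 51% of the variance at r = 0.2, 0.5 or 0.7. The gain thus runs from negligible to about half, and the article gives no correlation to narrow it. Any larger saving quoted for averaging several visits also rests on an assumed correlation pattern across the transplant.

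Total blood loss is measured once and has no preoperative value, so neither the primary analysis nor its sample size is affected.

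**What to change.** First reconcile the postoperative laboratory visits in Course of the study with those in the visit schedule, which differ on POD 5.

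Then add to Statistical design that each of Hb, INR, PTT and platelet count is compared between each device and control with the preoperative value as a covariate. This can be ANCOVA at one visit, or a mixed model over the postoperative visits, on the log scale where the variable is skewed. Prespecify one time point or summary per variable as the test, and report the other visits descriptively. That gives 4 variables × 2 contrasts = 8 tests. An average over the visits to POD 10 is one possible summary, not a required one; it could dilute an early difference, so the choice should follow the question the investigators want answered.

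The cost is wording only, with no new patients, visits or samples. The small downside is a modelling assumption: a linear relation with the preoperative value and, for the mixed model, a within-patient correlation structure, which can be left unstructured.
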